### Psychometric measures

2.5

#### Primary outcomes

2.5.1

##### Texas Revised Inventory of Grief (TRIG)

2.5.1.1

This self-report measure quantifies the severity of normal grief (59). In this trial, only one scale (the Present Feelings Scale, PFS) was used to assess the participant’s emotional state. This 13-item scale is scored on a 5-point Likert-type scale (from 1 = ”completely false” to 5 = ”completely true”) ranging from 13 to 65. Scores up to 39 (TRIG ≥ 40; above the 50th percentile), are defined as severe grief (60). The TRIG has been shown to have adequate psychometric properties, with the PFS having a Cronbach’s coefficient alpha value of.90 (61).

##### Traumatic Grief Inventory Self-Report (TGI-SR)

2.5.1.2

A measure designed to assess markers of grief disorder as defined by the ICD-11 and the DSM- 5, using PGD criteria (62). This questionnaire focuses on a total of 18 symptoms experienced during the preceding month, assessed on a 5-point Likert-type scales (from 1 = “never” to 5 = “always”). A total score of ≥ 59 identifies those meeting criteria for PGD-caseness. Cronbach’s alphas of the TGI-SR in the patient sample were.95 (all 18 items),.95 (17 PCBD items), and.93 (11 PGD items).

#### Secondary outcomes

2.5.2

##### Posttraumatic Growth Inventory‐Short Form (PSGI-SF)

2.5.2.1

This questionnaire measures the degree of positive change experienced in the aftermath of a traumatic event (63, 64). The PSGI-SF is a 10-item self-report measure scored on a 6‐point Likert scale (from 1= “no change” to 6 = “a high degree of change”). The five subscales are: (1) relating to others, (2) new possibilities, (3) personal strength, (4) spiritual change, and (5) appreciation of life. Total scores ≥ 32 indicate probable personal growth (65). The internal consistency coefficient of the questionnaire is.86 -.89 (66).

##### World Health Organization Quality of Life-BREF (WHOQOL -BREF)

2.5.2.2

This questionnaire is a shorter version of the original WHOQOL-100 (67). The measure was designed to assess quality of life in four different areas: physical health, psychological health, social relationships, and environment. For this study, only the first three scales were used. The 24-item questionnaire is scored on a 4–20 scale, with higher scores indicating a better quality of life. The scale has been shown to have adequate psychometric properties, with Cronbach’s coefficient alpha values ranging from.68 to.82 (68).

#### Measures of potential mediators

2.5.3

##### The Integration of Stressful Life Experiences Scale-Short Form (ISLES-SF)

2.5.3.1

This measure involves a self-assessment of “meaning made”, as the successful outcome of meaning-making after stressful life experiences (69, 70). ISLES-SF is a 6-item version of the original 16-item measure, and it relies on a 5-point Likert response scale (from 1 = “strongly disagree” to 5 = “strongly agree”). Scores above 14 on the ISLES-SF have been found to reflect clinically significant functional impairment in family, occupational and social contexts (71).The scale has a validated bi-factorial structure, permitting overall assessment of challenges to meaning-making, as well as scoring of two subscales: (1) *Footing in the World* (a measure of personal disorientation following loss) and (2) Comprehensibility (an index of ability to make sense of the experience; 72). The ISLES-SF has shown to have strong psychometric properties, with a Cronbach’s coefficient alpha value of.96 (73).

##### Acceptance and Action Questionnaire (AAQ-II)

2.5.3.2

This is a unidimensional scale to assess psychological flexibility (74, 75). The measure relies on a 7-point Likert-type scale (from 1 =“ never true” to 7 = “always true”). The total score is calculated adding all individual scores, with lower scores corresponding to greater psychological flexibility. In terms of psychometric properties, the AAQ-II has good validity and reliability with the mean Cronbach’s alpha being.84

##### Self-Concept Clarity Scale (SCS)

2.5.3.3

This 12-item scale measure the clarity and cohesiveness of the person’s self-concept (76). Self-concept clarity is measured on a 5 point-Likert scale (from 1= “strongly disagree” to 5 = “strongly agree”), with higher scores corresponding to greater self-concept clarity. The SCS has been shown to have adequate psychometric properties, with a Cronbach’s coefficient alpha value of .86.

#### Measures of subjective effects

2.5.4

##### The Altered State of Consciousness Rating Scale (5D-ASC)

2.5.4.1

This is a visual-analogue 94-item scale assessing five key dimensions of altered states of consciousness independently of their etiology (77). In this study, the 42-item version will be used (78), comprised of five different dimensions: (1) Oceanic Boundlessness, (2) Anxious Ego, (3) Visionary Restructuralization, (4) Auditory Alterations, and (5) Reduction of Vigilance (RV). The outcomes of the 5D-ASC data are percentage scores of maximum absolute scale values. This 42-item version has shown to have adequate psychometric properties, with Cronbach’s coefficient alpha of.83 for the 11-factorial structure (78).

##### Acceptance/Avoidance-Promoting Experiences Questionnaire Scale (APEQ)

2.5.4.2

This psychometric instrument has been designed to measure experiences related to acceptance and avoidance, that occur during a psychedelic-induced altered state of consciousness. The questionnaire is self-reported and comprises 32 items, divided into two main scales: (1) the Acceptance-Related Experience (ACE) scale and the (2) Avoidance-Related Experience (AVE) scale, as well as two ancillary scales: Introspection and Interaction. The Acceptance-Related Experience (ACE) scale encompasses the subscales (1.1) Accepting Response, (1.2) Pro-Acceptance Insights, and (1.3) Relief. The Avoidance-Related Experience (AVE) scales comprise the subscales (2.1) Pro-Avoidance Insight, (2.2) Avoidant Response, and (2.3) Distress subscales. Cronbach’s coefficient alphas are.92 for the ACE scale,.89 for the AVE scale,.84 for the Introspection scale, and.75 for the Interaction scale.

#### Level of Satisfaction and Adverse Effects Assessment (S.A)

2.5.5

In the post-assessment, participants will complete a survey comprising two satisfaction-related questions: (1) “To what extent are you satisfied with the therapeutic support provided during the psychotherapy sessions?”; (2) “To what extent are you satisfied with the ayahuasca sessions?”. Responses will be rated using a 5-point Likert-type scale (from 1 = “Very dissatisfied” to 5 = “Very satisfied”)

Adverse effects will be evaluated using the following questions: (3) “Have you experienced any negative effects from the psychotherapeutic sessions?”; (4) “Did you experience any negative effects during the ayahuasca session?”; (5) “Did you experience any negative effects in the week following the ayahuasca session?”. Responses will be categorized as: (1) No, (2) Uncertain, or (3) Yes.

Each of these questions will be followed by an open-ended prompt encouraging participants to provide further details about their responses.

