### Procedure

2.3

Participants will be recruited through the newsletter, webpage, and social media accounts of the Beckley Foundation, Beckley Med, MIND Foundation and the International Center for Ethnobotanical Education, Research and Service (ICEERS), all of them European institutions dedicated to psychedelic research and education. Upon receiving the request to participate in the trial, the participant will be prompted to complete a short online questionnaire to screen for inclusion criteria. Those who meet the inclusion criteria will attend a video-call interview with the principal investigator (DG) to learn more about what their participation would entail and to screen whether any exclusion criteria are met. They will also be informed about the need to verify their blood pressure range with a general practitioner to prevent potential ineligibility, given that blood pressure measurement is taken on-site before each ayahuasca session. Then, those who are eligible will provide informed consent. Assessments will be conducted online at baseline (T0), during treatment (T1 and T2), at post-intervention (T3), and at 3-month follow-up (T4) (see **Figure 1**).

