**Figure 1 f1:**
[figure not shown]
Flow-chart of the recruitment procedure.

Participants in the A-MR and MR group will undergo a 9-session online psychotherapy process, starting within 2 weeks after the baseline assessment is completed. Only those in the A-MR group will participate in up to two onsite ayahuasca sessions throughout the therapeutic process, preceded by an online preparation session, and followed by a 50-minute MR online integration session during the week after each ayahuasca experience. For ethical reasons, participants in either control group (MR or NT) have the option to participate in two ayahuasca sessions over a single weekend, once follow-up assessment is completed, if their grief symptom severity are still significant (TRIG ≥ 40), proceeded by a preparation session and followed by two integration sessions to process the experience. **Table 1** shows the measures used at each of the time points.

**Table 1 T1:** Enrolment, intervention, and assessment schedule (SPIRIT).

	STUDY PERIOD									
	Enrolment	Baseline	Allocation	Treatment					Post-treatment	Follow-up
TIMEPOINT		(T0)		Phase 1	Ayahuasca (T1)	Phase 2	Ayahuasca (T2)	Phase 3	(T3)	(T4)
ENROLMENT										
Eligibility screen	x									
Informed consent	x									
Allocation			x							
INTERVENTION										
MR				x		x		x		
NT										
A-MR				x	x	x	x	x		
ASSESSMENT										
TRIG	x	x							x	x
TGI-SR		x							x	x
PSGI-SF		x							x	x
WHO-qol-BREF		x							x	x
AAQ-II		x							x	x
ISLES-SF		x							x	x
SCS		x							x	x
5D-ASC					x		x			
APEQ					x		x			
SA									x	

MR, Meaning Reconstruction Therapy; NT, No treatment; A-MR, Ayahuasca-assisted Meaning Reconstruction Therapy; TRIG, Texas- Revised Inventory of Grief; TGI-SR, Traumatic Grief Inventory self-report; PSGI-SF, Post-traumatic Growth Inventory‐Short Form; WHO-qol-BREF, World Health Organization Quality of Life-Brief; AAQ-II, Acceptance and Action Questionnaire II; ISLES-SF, Integration of Stressful Life Experiences Scale Short-Form; SCS, Self-concept clarity Scale; 5D-ASC, Altered State of Consciousness Rating Scale; APEQ, Acceptance/Avoidance-Promoting Experiences Questionnaire Scale; SA, Level of Satisfaction and Adverse Effects

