### Sample size

2.4

Given that no comparative trials analyzing the therapeutic effect of PAP on reduction of grief symptoms has been published to date, sample size was calculated based on the results of González et al. (35) observational study. The observed Cohen’s d (0.84) for the study group between the baseline and the 15^th^-day-post-treatment assessment, and TRIG measurement correlation of 0.55, were used to estimate the sample size for this study. Therefore, sample size was calculated based on the assumption of a between groups differences at post-treatment of at least 9.4 points (TRIG score) in mean change between the A-MR and the NT groups. Sample size with power of 0.90 and an alpha of 0.05 was calculated using pwrss R package version 0.3.1 (58). To find at least the above effect size, a total sample of 69 participants is needed, but as drop-out rate of 20% were considered, 84 participants will be recruited.

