#### Ayahuasca-assisted Meaning Reconstruction therapy

2.7.2

The experimental group intervention (A-MR) adheres to the same online Meaning Reconstruction Therapy protocol, with the incorporation of up to two onsite ayahuasca sessions following phase 1 (session 3) and phase 2 (session 6) (see **Table 2**). The first ayahuasca session is preceded by a preparatory online group session (after session 1) and is followed by an online individual integration session during the week after the ayahuasca administration. This design is based on the contemporary structure of PAP, which typically involves a three-stage framework encompassing preparation, facilitation, and integration (104).

**Table 2 T2:** Ayahuasca-assisted meaning reconstruction protocol (A-MR).

Phases	Psychological content	Session	Techniques
Opening	Fostering therapeutic alliance; Exploring potential difficulties; Psychoeducation: Dual model of grief coping	1	
On-line preparation of ayahuasca session*			
**Phase 1:** The “event story” of the loss	Processing traumatic or stressing memories, and finding meaning in loss and in life	2	Narrative retelling
		3	Narrative retelling
First ayahuasca session*			
Integration of ayahuasca experience*			
**Phase 2:** The “back story” of the relationship with the deceased	Restoring attachment security through reconstructing a bond with the deceased and/or processing unfinished business	4	Introducing the deceased
		5	Imaginal conversation with the deceased
		6	Internal representation of the deceased’s reconstruction
Second ayahuasca session*			
Integration of ayahuasca experience*			
**Phase 3:** The “personal story” of self	Reorganizing one’s identity and life orientation as a survivor	7	Bull’s-Eye Values Survey
		8	Bull’s-Eye Values Survey
Ending	Summary of the psychotherapeutic process	9	

*Excluded in the MR intervention protocol.

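### The self-report questions on ayahuasca harms are asked once, at T3, with one answer per time window for up to two sessions, so answers cannot be reliably tied to a session and dosed participants who miss T3 may not be counted

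*Protocol article*

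**What the plan says.** - **Timing of the survey.** Section 2.5.5: "In the post-assessment, participants will complete a survey comprising two satisfaction-related questions". The numbering continues with three adverse-effects questions (items 3 to 5). Table 1 has a row for this survey (legend: "SA, Level of Satisfaction and Adverse Effects") with a single mark, under T3, and none at T1, T2 or T4.
- **The two ayahuasca items.** Item 4: "Did you experience any negative effects during the ayahuasca session". Item 5: "Did you experience any negative effects in the week following the ayahuasca session". The answer is no, uncertain or yes. Section 2.5.5 adds: "Each of these questions will be followed by an open-ended prompt encouraging participants to provide further details about their responses".
- **Number of sessions.** Section 2.7.2 gives A-MR "up to two onsite ayahuasca sessions following phase 1 (session 3) and phase 2 (session 6") of a nine-session weekly therapy. Item 2 of the same survey, on satisfaction, speaks of the ayahuasca sessions in the plural; items 4 and 5 do not.
- **Assessments that already exist.** Section 2.3: "Assessments will be conducted online at baseline (T0), during treatment (T1 and T2), at post-intervention (T3), and at 3-month follow-up (T4"). Table 1 places the 5D-ASC and the APEQ at T1 and T2. An online integration session falls in the week after each ayahuasca session.
- **Other observation of harm.** Section 2.7.2.2 describes medical supervision for at least 12 hours, vital-sign monitoring in participants with adverse effects, and a physician-rated PANSS-EC at 24 hours for all participants.
- **Attrition.** Section 2.4: "drop-out rate of 20% were considered", which takes the target from 69 to 84.

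**The concern.** The article's own background reports distress during acute effects, a need for medical support in 2.3% of surveyed users and rare psychotic episodes. What participants say about harm is therefore an important output of the trial.

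Two features of the schedule weaken it. First, one late answer has to cover two exposures. For someone who had two sessions, the week after the session is not one definite week, and a yes cannot be placed reliably at the first or second exposure. Second, the answer depends on reaching T3. People who stop because a session went badly are the ones a post-treatment survey is most likely to miss. If that happens, the reported proportion describes those who stayed rather than those who were dosed.

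**Working it through.** **1. Recall period.** Therapy sessions are weekly. The first ayahuasca session follows therapy session 3 and the second follows session 6.
- First ayahuasca session to T3: sessions 4 to 9 intervene. That is six weekly sessions, so at least about 6 weeks. If each of the two integration sessions takes a week of its own, it is about 6 + 2 = 8 weeks.
- Second ayahuasca session to T3: sessions 7 to 9 intervene, so at least about 3 weeks, or 3 + 1 = 4 with its integration week.

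This step and the merging of the two sessions need no assumption about drop-out.

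**2. The plan's own attrition figure.** 69 / 3 = 23 per arm. 23 × 1.2 = 27.6, rounded up to 28, and 3 × 28 = 84, which reproduces the stated target. (69 / 0.8 = 86.25, or 87, does not.) The planned loss is 84 − 69 = 15, or 5 per arm with equal arms: 5/28 = 17.9%. Applying 20% to 28 gives 5.6.

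The 20% is a trial-wide planning figure with no timing. It may include people who leave before the first ayahuasca session (not exposed) and people lost after T3 (already asked). The A-MR rate could also differ from the trial-wide one.

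**3. Effect on the reported rate.** Let m be the share of dosed participants not asked, p the harm rate among those asked, and q the rate among those not asked.

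True rate = (1 − m)p + mq. Error of the survey rate = p − true rate = m(p − q).

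The documents give no value for p or q and no value of m for dosed participants. With m = 0.20 as an assumed ceiling, the true rate is 0.8p + 0.2q:

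| p (assumed) | q = 0 | q = p | q = 0.5 | q = 1 |
|---|---|---|---|---|
| 5% | 4% | 5% | 14% | 24% |
| 10% | 8% | 10% | 18% | 28% |
| 20% | 16% | 20% | 26% | 36% |
| 30% | 24% | 30% | 34% | 44% |
| 60% | 48% | 60% | 58% | 68% |

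In whole persons, with 5 of 28 not asked and p = 10% of the other 23 (2.3 expected), the range is 2.3/28 = 8.2% to 7.3/28 = 26.1%.

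The survey rate is too low only if q exceeds p. It is unbiased at q = p and too high if q is below p. The largest understatement is 0.20(1 − p), or 18 percentage points at p = 10%. The largest overstatement is 0.20p, or 2 points.

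**4. What the other measures reach.**

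| Measure | When | What it covers | Per session? | Covers the following week? |
|---|---|---|---|---|
| PANSS-EC | 24 h after ingestion | Excitement/agitation, physician-rated | Yes, as described | No |
| APEQ, 5D-ASC | T1, T2 | Acute experience, including distress and anxiety dimensions | Yes | No |
| Supervision, vital signs | Around the session | Clinical observation | Yes | No |
| Survey items 4 and 5 | T3 | Any negative effects, self-report | No | Yes, by recall |

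Only the survey asks about negative effects in general and about the week after, and it does so only at T3.

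**The case against.** A reader might infer that participants who leave early are never asked and that the harm rate is therefore understated. The documents do not support either step. Nothing says that leaving treatment ends assessment, and Section 2.6 names intent-to-treat as an option, so someone who stops therapy may still complete T3. Understatement also requires more harm among those not asked than among those asked. That is plausible, but no figure in the article establishes it.

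Nor should the survey be read as the trial's only record of harm. The 24-hour PANSS-EC does not depend on reaching T3, and the APEQ and 5D-ASC give session-specific data on difficult reactions. These measures are narrow, but they would reach someone who left after the first session. There are also two ayahuasca items, one per time window, and each has an open prompt that may let some participants say which session they mean. An optional free-text remark is not a reliable way to attribute an answer, so the merging problem is reduced but not removed.

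The magnitude is open to challenge too. Section 2.7.2.2 calls nausea and vomiting common, so the proportion reporting any negative effect could be well above 10%. With 60% among those asked and 80% among those not asked, the rate moves only from 60% to 0.8 × 60% + 0.2 × 80% = 64%.

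Finally, a journal article may leave adverse-event logging and procedures at withdrawal to the full protocol. That is accepted, and their absence is not part of this point. What stands is what the article does fix: the survey's time point, in both the text and the schedule table, and the wording of items 4 and 5.

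**Conclusion.** The point holds as a weakness in the stated schedule. Items 4 and 5 are asked once, at T3, with one answer per time window for up to two sessions, and the first session lies at least about six weeks back. Session attribution and recall suffer whatever the drop-out.

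The survey-based harm rate may also be biased by who completes T3, probably downward if harm drives drop-out. The size is unknown. With at most 20% of dosed participants unasked and 10% of those asked reporting harm, the true rate lies between 8% and 28%. Both inputs are assumptions, and the 20% borrows a trial-wide figure that is not specific to A-MR or to the period between first dose and T3. The efficacy analyses are not affected. The change is worth making before the sessions take place, because a timely answer cannot be recovered later.

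**What to change.** In Section 2.5.5 and Table 1:
- Add item 4 to the existing online T1 and T2 assessments, so that each session has its own answer.
- Add item 5 as a short self-report at the first scheduled contact at least one week after each ayahuasca session. The integration session falls inside the week that item 5 asks about, so it is too early. Keeping it as self-report avoids turning it into an answer elicited by the therapist.
- Keep the T3 survey as well, so that effects recognised later are still recorded.
- Report negative effects per session, with everyone who took at least one dose as the denominator, and state how many did not answer.

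The cost is about a minute of participant time per contact, at assessments and contacts that already take place. The proposal changes only when questions are asked and how answers are reported; it touches no dose, schedule of treatment or clinical rule.

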The first phase is focused on the employment of non-directive narrative retelling to help the participant revisit the story of the loss, and the stressful or traumatic memories connected to it (37, 96, 97). This technique, when conducted in a safe and low-avoidance setting, can enable the bereaved to reconstruct a coherent narrative of the loss and its implications through introspection and deliberative processing and integration of its meaning. When necessary (e.g. when significant anxiety is present), relaxation and/or mindfulness techniques are introduced to manage activation and foster self-regulation.The second phase is focused on promoting a secure attachment with the deceased (98), addressing unfinished business, or processing anger and guilt (37). Different techniques are employed to help reconstruct the internal representation of the deceased, such as introducing the deceased (99) and engaging in an imaginal conversation with them (100). When appropriate, and desired by the participant, a key aim is to establish and maintain a constructive continuing bond with the deceased (101).The third and last phase prioritizes the reconstruction of the bereaved person’s sense of self and their future as a survivor (7, 102). The Bull’s-Eye Values Survey (BEVS), a contextual form of behavioral activation and values clarification, is employed to restore the participant’s life orientation without the deceased (103).

Participants will complete a 50-minute session on a weekly basis, conducted online through a secure videoconference platform in compliance with HIPAA guidelines. Every therapist in the trial is a licensed psychologist, and all of them have received specialized training in the delivery of the treatment protocol. Furthermore, they have access to clinical supervision provided by DG and PS upon request. All the therapists have prior experience in PAP and/or psychedelic integration and are affiliated with the Spanish Society of Psychedelic Medicine (SEMPSi).

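### The only adverse-effects questionnaire described is given once, at T3, weeks after each ayahuasca session, with one answer for up to two exposures and none from anyone without a T3 assessment

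*Protocol article*

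**What the plan says.** Section 2.5.5 (Level of Satisfaction and Adverse Effects Assessment) fixes both the instrument and its time: "In the post-assessment, participants will complete a survey comprising two satisfaction-related questions", followed by three questions on adverse effects. Item 3 asks about negative effects of the psychotherapy, item 4 about negative effects during the ayahuasca session, and item 5 reads "Did you experience any negative effects in the week following the ayahuasca session". Answers are no, uncertain or yes, each with an open-ended prompt.

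In Table 1 (section 2.3) the row for this survey, defined in the footnote as "SA, Level of Satisfaction and Adverse Effects", carries one mark, under T3. There is none at T1, T2 or T4. Section 2.3 lists assessments "during treatment (T1 and T2), at post-intervention (T3), and at 3-month follow-up (T4", after the baseline at T0, and Table 1 shows that the 5D-ASC and APEQ are already collected at T1 and T2.

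On timing, section 2.7.1 states "Participants will complete a 50-minute session on a weekly basis". Section 2.7.2 provides "up to two onsite ayahuasca sessions following phase 1 (session 3) and phase 2 (session 6" of nine, and the first of these "is followed by an online individual integration session during the week after the ayahuasca administration"; section 2.3 and Table 2 place such an integration session after both. On attrition, section 2.4 says "but as drop-out rate of 20% were considered, 84 participants will be recruited".

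**The concern.** Items 4 and 5 ask about narrow windows, the session itself and the week after it, but they are put to participants weeks after those windows have closed. Both items use the singular, while the satisfaction question in the same survey uses the plural. A participant with two exposures therefore gives one answer, which can be assigned to neither.

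The survey also depends on a T3 assessment being made. If people with bad experiences are more likely to be lost before T3, the survey will show a lower rate of negative effects than occurred among those exposed. The article's introduction itself cites acute distress, a small proportion of users needing medical support, and isolated psychotic episodes. Its discussion makes a future trial conditional on the intervention proving feasible and effective. A harms count that leans toward safety would be a poor basis for that step.

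**Working it through.** **1. Interval from exposure to the survey.** The article states no interval, so I derive it. Put session 1 on day 0 with weekly sessions. Session 3 is then on day 14. Ayahuasca sessions start on a Saturday (section 2.7.2.1), which falls between day 15 and day 20, before the next weekly slot on day 21. The article does not say whether the integration session is additional to the weekly sessions or takes a weekly slot, so both readings are shown. Session 9 is the earliest point at which T3 could follow.

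| Reading | Session 6 | Session 9 | First ayahuasca to session 9 | Second ayahuasca to session 9 |
|---|---|---|---|---|
| Integration is extra | day 35 | day 56 | 56 − 20 = 36 to 56 − 15 = 41 days (5.1 to 5.9 weeks) | 56 − 41 = 15 to 56 − 36 = 20 days (2.1 to 2.9 weeks) |
| Integration takes weekly slots | day 42 | day 70 | 70 − 20 = 50 to 70 − 15 = 55 days (7.1 to 7.9 weeks) | 70 − 48 = 22 to 70 − 43 = 27 days (3.1 to 3.9 weeks) |

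The range is about 5 to 8 weeks for the first exposure and 2 to 4 weeks for the second. T3 adds an unstated time.

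**2. How many may give no answer.** The recruitment figure is reproduced per arm: 23 × 1.2 = 27.6, rounded up to 28, and 3 × 28 = 84, as section 2.4 states. With equal arms (an assumption), the plan allows for 28 − 23 = 5 losses in A-MR; a literal 20% of 28 is 5.6. This is a ceiling on exposed people missed, because someone who leaves before the first ayahuasca session, or who fails the on-site blood-pressure check, was never exposed.

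**3. What that loss could do.** The harm rates are assumed, since the document gives none. Let a fraction 0.2 of exposed participants have no T3 answer, let the rate among responders be p, and let the rate among those lost be k times p.

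- True rate = p(0.8 + 0.2k).
- Share of affected people missed = 0.2k / (0.8 + 0.2k).
- k = 1: 0.2/1.0 = 20% missed. The count is short, but the rate among responders is unbiased.
- k = 2: 0.4/1.2 = 33% missed. With p = 10%, the true rate is 12%.
- k = 3: 0.6/1.4 = 43% missed. With p = 10%, the true rate is 14%.

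These treat every loss as exposed, so they are upper values for each k.

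**4. What else observes harm.** A physician rates the PANSS-EC 24 hours after ingestion in all participants (section 2.7.2.2.3). It is one excitement component at one time point. Medical supervision lasts at least 12 hours. The APEQ at T1 and T2 has a Distress subscale, but it concerns experiences during the altered state (section 2.5.4.2). The integration session falls in the right week, but it is described as therapy, not as a record of adverse effects. None of these records negative effects over the week after each session.

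**The case against.** The strongest reply is that the article describes other safety observation, and that routine adverse-event recording, contact with people who withdraw, and reporting denominators usually sit in the full protocol, which is not shown. That stands. It would be wrong to infer that nobody watches for harm, that early leavers contribute no safety data, or that no adverse-event log exists. The point is confined to a choice the article does fix: the content and timing of this one questionnaire.

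Several stronger readings are tempting but unsupported:

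- **Survey at least six weeks after the first session and three after the second.** That counts from therapy session 3 or 6 to session 9. Counted from the ayahuasca Saturday, the minimum to session 9 is 5.1 and 2.1 weeks.
- **People who stop treatment never answer.** The article does not say that they miss T3. Section 2.6 allows an intent-to-treat analysis, and since participants have up to two ayahuasca sessions, someone who declines the second may stay in the trial and answer at T3.
- **Every lasting harm vanishes because all those affected leave.** This is an invented extreme, not something the plan's figures imply.
- **The lack of an item for the no-treatment arm is a flaw.** Questions about effects of a treatment cannot apply there. Item 3 serves both therapy arms, and grief and quality-of-life scores are taken in all arms at T3 and T4.

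The open-ended prompts could let a participant say which session was meant. That helps, but it leaves attribution to chance.

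**Conclusion.** The concern holds as a point about one instrument. The only adverse-effects questionnaire described is late relative to the windows it asks about (about 5 to 8 weeks and 2 to 4 weeks to session 9, with T3 later), gives one answer for up to two exposures, and yields nothing from anyone without a T3 assessment. That is up to about 5 of 28 A-MR recruits if arms are equal and drop-out is as planned.

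The direction of bias is conditional. If loss is unrelated to harm, the rate among responders is not distorted by drop-out, though recall error and the pooling of sessions remain. If loss is related to harm, the survey leans toward apparent safety. A reader might infer that harms will certainly be under-counted in the trial as a whole; the document does not support that, because other observation is described and fuller recording may exist elsewhere. The change is still worth making, since better-timed contacts are already in the schedule.

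**What to change.** - Ask item 4 (effects during the session) with the existing T1 and T2 questionnaires, one answer per session.
- Ask item 5 (the following week) about one week after each session, for example by a short online form around the integration session. It should not simply move to T1 and T2: the article states no delay for these, and if they are completed promptly the week in question has not yet passed.
- Send both items to exposed participants who stop early.
- Keep the T3 survey as it is.
- Report rates with all exposed participants as the denominator, and state how many gave no answer.
- Edit the survey's row in Table 1 to match.

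The cost is a few extra items per A-MR participant, one short form after each session, and a table edit. No clinical rule changes.
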